### Quality control and cohort maintenance

CCs will assess questionnaire responses for completeness and accuracy. If deficiencies are identified, participants will be requested to re-complete the forms. To minimize loss to follow-up, incentives such as free clinic visits, partial reimbursement of examination fees, and expedited appointments will be provided. CCs will regularly disseminate healthcare tips, educational materials, and reminders via WeChat. The cohort manager (CM) will be available for direct online medical consultations. Participants lost to follow-up will be contacted via phone or WeChat to encourage continued participation.

### Items of follow-up visits

Follow-up assessments in the vNOTESTEP study will include standardized scales, questionnaires, and clinical investigations. The Chinese versions of all questionnaires used in this study were professionally translated and validated via independent back-translation. The following measures will be used to evaluate postoperative outcomes of vNOTES and TU-LESS:

**Body Image Questionnaire (BIQ)**: An eight-item scale assessing postoperative body image and cosmetic perception. Items 1–5 evaluate patients’ self-perception and satisfaction with their appearance, while items 6–8 assess satisfaction with the surgical scar [36, 37]. BIQ will be administered at the 1-month follow-up visit.**Visual Analog Scale (VAS)**: A validated tool for pain assessment, consisting of a 10 cm-long scale ranging from ‘no pain’ to ‘extreme pain.’ Patients will indicate pain intensity on postoperative days 1, 2, and 3. Pain scores will be classified as: <1 cm (painless), 1–3 cm (mild), 4–6 cm (moderate), and 7–10 cm (severe). CCs will record and upload VAS scores to the study database.**Female Sexual Function Index (FSFI)**: A validated 19-item scale assessing six domains of sexual function, including libido, arousal, lubrication, orgasm, satisfaction, and pain [38]. A total score < 26.5 indicates impaired sexual function [39]. The FSFI will be administered preoperatively and postoperatively at 3 and 6 months. Since sexual activity is contraindicated for one month following vNOTES to allow vaginal incision healing, FSFI will not be assessed at earlier time points [40]. **Pregnancy and delivery outcomes**: A self-designed **Pregnancy and Delivery Questionnaire (PDQ)** collecting postoperative gestational history (see Appendix 1). The PDQ includes seven questions regarding pregnancy status, conception method, delivery mode, parity, vaginal laceration, and incisional hernia (IH). This will be administered at all follow-up visits except the 1st month. Patients will be encouraged to undergo pregnancy monitoring and delivery at CWCCH to facilitate comprehensive data collection via HIS.**Incisional complications**: At each follow-up visit, patients will undergo gynecologic physical examinations to assess for IH. Patients with suspected IH (i.e., those experiencing incisional pain or a bulge) will be referred for imaging investigations, including ultrasound, computed tomography (CT), or magnetic resonance imaging (MRI). Diagnosed IH cases will be treated appropriately, and CCs will document relevant findings in the study database.

**Fig. 1 Fig1:**
[figure not shown]
Schematic diagram presenting the flowchart of the vNOTESTEP study. Abbreviations: vNOTESTEP, Transvaginal Natural Orifice Transluminal Endoscopic Surgery for Tubal Ectopic Pregnancy study; vNOTES, Transvaginal Natural Orifice Transluminal Endoscopic Surgery; TU-LESS, transumbilical laparoendoscopic single site; IH, incisional hernia

**Fig. 2 Fig2:**
[figure not shown]
Schedule of enrolment, interventions, and assessments of the vNOTESTEP study. Abbreviations: vNOTESTEP, Transvaginal Natural Orifice Transluminal Endoscopic Surgery for Tubal Ectopic Pregnancy study; vNOTES, Transvaginal Natural Orifice Transluminal Endoscopic Surgery; TU-LESS, transumbilical laparoendoscopic single site; VAS, Visual Analog Scale; BIQ, Body Image Questionnaire; PDQ, Pregnancy and Delivery Questionnaire; IH, incisional hernia

### Data collection and management

Gynecologists from inpatient and outpatient departments will document preoperative and surgical assessments in the HIS. Face-to-face interviews or phone calls will be conducted to supplement data collection. A gynecologic laparoendoscopic specialist will serve as the CM, overseeing cohort management and CCs’ responsibilities. CCs will obtain informed consent, conduct follow-up visits, and facilitate data entry into the study database.

To minimize bias, assessors will remain blinded to patients’ surgical allocation. The CM will ensure that surgical approach details are concealed before CCs collect perioperative and follow-up data. Randomization will also be applied to CCs’ work assignments. A secure, self-built database will store all study data.

### Baseline information

Baseline demographic and clinical characteristics of enrolled participants will be recorded in the HIS, including age, education level, occupation, household income, lifestyle factors (smoking, alcohol consumption), comorbidities, medication history, reproductive and surgical history, height, weight, and body mass index (BMI).

### Perioperative assessment and short-term postoperative outcomes

#### Primary short-term outcome

Completion of surgery using the allocated technique is Primary short-term outcome that we will focus on. We will also conduct a detailed analysis of cases requiring surgical conversion, including the reasons for conversion, the type of surgical techniques converted into, as well as the specific complications and their severity.

#### Secondary short-term outcomes

Intraoperative complications (e.g., unintended organ injury), blood loss volume, reasons for surgical conversion, operative duration, hospital stay length, and postoperative complications (e.g., bleeding, wound infection, pain, urinary retention, febrile morbidity). Perioperative complications will be classified according to the Clavien–Dindo system [41]. 

### Long-term postoperative outcomes

#### Primary long-term outcomes

Pregnancy and vaginal delivery outcomes and incidence of incisional wound complications.

#### Secondary long-term outcomes

Cosmetic satisfaction, impact on sexual function, pregnancy outcomes, and IH occurrence. These outcomes will be evaluated according to the follow-up schedule outlined in Figs. 1 and 2.

### Economic evaluation

A cost-effectiveness analysis will compare hospitalization, surgery, and consumable costs between vNOTES and TU-LESS. Findings will support guideline development and inform patient decision-making.

### Statistical analysis

Statistical analyses will be conducted using SPSS (Version 25.0) and R. Continuous variables will be analyzed using t-tests or Mann–Whitney tests, with results presented as means ± standard deviations for normally distributed data and medians with interquartile ranges for non-normally distributed data. Categorical variables will be analyzed using chi-square or Fisher’s exact tests. To mitigate bias, statistical techniques such as propensity score matching (PSM), stratification, multivariate analysis, Cox regression, and generalized estimating equations (GEE) will be employed as necessary. A binary logistic regression analysis will also be conducted to assess the risk factors for surgical conversion, incorporating variables that demonstrate a significant statistical difference in the univariate comparisons. Statistical significance will be set at *p* < 0.05.

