## Methods

### Study design

The vNOTESTEP study is a single-blind RCT designed to evaluate the perioperative and long-term postoperative outcomes of vNOTES compared withTU-LESS in patients with tubal ectopic pregnancy. Considering ethical concerns and the low likelihood that patients would be unaware of their incision site, this study will adopt a single-blind design, with blinding applied only to the outcome assessors (OAs) and not to the patients. After obtaining informed consent from each participant, preoperative assessments will be conducted. Following randomization, salpingectomy will be performed via either vNOTES or TU-LESS approach. The primary outcomes include perioperative outcomes like surgical conversion, change of postoperative sexual function, pregnancy, and vaginal delivery. The study will be conducted at CWCCH, a university teaching hospital and regional training center for vNOTES, spanning from 2024 to 2030, with two years allocated for recruitment and three to five years for follow-up.

CWCCH has a highly experienced team of approximately 20 gynecologic endoscopic specialists, who collectively perform 500–600 vNOTES and 1000–2000 TU-LESS procedures annually. Randomization and grouping will be performed by a cohort manager (CM) using a computer-generated system after stratification. To maintain blinding, identifiable patient information will be removed. Outcome assessors (OAs) will be blinded to patient allocation, with OA1 responsible for evaluating incisional wounds and OA2 assessing non-incisional wound-related perioperative and postoperative outcomes. Both the umbilical and vaginal incisional sites will be dressed uniformly to achieve blinding during hospitalization. Patients will not be informed of the type of surgery they undergo either preoperatively or postoperatively to maintain blinding as much as possible. In cases of severe incisional complications, blinding may be lifted for appropriate medical intervention. Information exchange between CM, OAs, and cohort coordinators (CCs) will be restricted until the study’s completion.

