### Study population

#### Sample size calculation

Sample size estimation was based on the NOTABLE cohort study [24]. Previous studies report a conversion rate for vNOTES in tubal ectopic pregnancies between 1.83% and 3.07%, suggesting a surgical success rate of approximately 95%.^34,35^A one-sided non-inferiority test was used to determine the sample size, assuming that vNOTES would remain a preferred option despite a potential 15% lower success rate compared to TU-LESS, which results in visible scarring. To achieve 85% power for non-inferiority with a 95% expected success rate in both groups, a total of 54 cases were required. Accounting for an anticipated 20% dropout rate, the final sample size was set at 72 participants, with 36 per group.

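### The stated default test for FSFI uses only women with a month-6 form, so month-6 harm is understated if loss after month 3 follows low scores and differs by arm

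*Protocol article*

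**What the plan says.** The Statistical analysis section sets a general rule: "Continuous variables will be analyzed using t-tests or Mann–Whitney tests". A list of further methods follows, offered as ways to mitigate bias, and it ends "multivariate analysis, Cox regression, and generalized estimating equations (GEE) will be employed as necessary". No outcome is attached to GEE, no working correlation or weighting is named, and the condition that would make it necessary is not given.

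FSFI is a repeated continuous score. Under Items of follow-up visits: "The FSFI will be administered preoperatively and postoperatively at 3 and 6 months".

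The Sample size calculation section anticipates some loss: "Accounting for an anticipated 20% dropout rate, the final sample size was set at 72 participants, with 36 per group". That allowance belongs to a calculation built on surgical success. It is not linked to a visit, an arm or FSFI.

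The rank of sexual function varies. Study design says "The primary outcomes include perioperative outcomes like surgical conversion, change of postoperative sexual function, pregnancy, and vaginal delivery", while Secondary long-term outcomes lists "Cosmetic satisfaction, impact on sexual function, pregnancy outcomes, and IH occurrence". The article's conclusion also names sexual function as a particular focus.

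**The concern.** A two-sample test at month 6 needs a month-6 value. A woman who completed the month-3 form and then left contributes nothing to it, although her month-3 score is in the database and is informative about the missing value. If absence at month 6 is unrelated to her score, only precision is lost. If women who did badly at month 3 are the ones who leave, those who remain look better than the arm as a whole.

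The vaginal incision is what might affect sexual function, and the Discussion concedes that patients can detect an umbilical incision. Loss related to the score and different between arms is therefore foreseeable, though the documents cannot show that it will happen. The error would run towards finding no harm, on an outcome that the trial was partly set up to examine.

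**Working it through.** **1. The plan's own figure.** There is no FSFI calculation to reproduce. The only relevant figure is the 20% dropout. Applied to 54 it gives 54/(1 − 0.20) = 67.5, so 68, whereas the stated 72 corresponds to a loss of 1 − 54/72 = 25%. That mismatch is a separate matter and nothing below depends on it. With 20% lost, 36 × 0.80 = 28.8 women per arm would have a month-6 score.

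**2. Inputs.**
- From the article: 36 per arm; FSFI at baseline, month 3 and month 6; 20% as an overall loss, used here only to illustrate loss at month 6.
- Assumed, because the article gives none of them: equal SD of 6 (or 5) at each visit; true difference of −3.0 points (vNOTES minus TU-LESS) at months 3 and 6; correlation ρ between months 3 and 6 of 0.4 to 0.75 (or 0.3 to 0.7); and the dropout mechanism.

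**3. Formula.** Suppose leaving before month 6 depends only on the month-3 score. In each arm let S be the amount by which the mean month-3 score of those who stay exceeds that of all women in the arm. With equal SDs the month-6 mean of those who stay is too high by ρ × S. So

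returners-only difference = −3.0 + ρ × (S for vNOTES − S for TU-LESS).

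**4. Score-driven loss in vNOTES only, SD 6, 20% lost in each arm.** S is 0 in TU-LESS. In vNOTES, S is about 1.04 points if the log-odds of leaving rise by 1 per SD of lower score, and about 1.57 if they rise by 2.
- Mildest: −3.0 + 0.4 × 1.04 = −2.58 (0.42/3.0 = 14% of the harm lost).
- Strongest: −3.0 + 0.75 × 1.57 = −1.82 (1.18/3.0 = 39% lost).

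Simulation agrees. A maximum-likelihood fit of both visits gives about −3.0 throughout, and GEE with exchangeable correlation gives about −2.9 to −3.0.

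**5. Loss alike in both arms.** If both arms have the same loss rate and the same dependence on score, the two S values are equal and the bias is zero. With random loss both are zero.

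**6. Second set of assumptions: SD 5, ρ 0.3 to 0.7, 20% missing overall, 400,000 simulated women per arm.** The true value is −3.0 in every row.

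| Loss before month 6 | Two-sample test, or independence GEE | Exchangeable GEE | Likelihood, both visits |
|---|---|---|---|
| Random | −3.01 to −2.98 | −3.01 to −2.99 | −3.01 to −2.99 |
| Same logistic rule in both arms (about 16% and 24% lost) | −2.90 to −2.77 | −2.99 to −2.97 | −3.01 to −2.98 |
| Score-driven in vNOTES only (20% and 20%) | −2.76 to −2.40 | −3.00 to −2.98 | −3.02 to −3.00 |
| Lowest fifth of all month-3 scores leave (about 12% and 28%) | −2.62 to −2.14 | −2.84 to −2.70 | −3.03 to −2.98 |

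The understatement in the first results column is about 3–8%, 8–20% and 13–29% in rows two to four. Independence GEE with arm-by-visit terms reproduces the two-sample figures exactly. The likelihood column used the true correlation. When the regression of month 6 on month 3 was estimated from the returners (SD 5 and SD 6 settings with logistic loss), the estimate was again about −3.0.

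**The case against.** The strongest reply is that the article never says how month-6 FSFI will be analysed. The analysis section is one general paragraph, GEE is listed in it, and model choice and missing-data handling are often left to an analysis plan that is not shown. Much of this stands. The absence of a missing-data section is no finding here. What remains is that the article does state a default for continuous outcomes, FSFI falls under it, and the better method is left to discretion.

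Several stronger readings are tempting and are not supported:
- **That GEE is equally confined to returners.** Only independence GEE is. With a non-independence working correlation, a leaver's month-3 score informs the month-6 estimate and most of the bias goes. Unweighted GEE is in general assured only when loss is completely random, which explains what is left in the extreme row of the table.
- **That the plan expects a fifth of women to lack a month-6 FSFI.** "Accounting for an anticipated 20% dropout rate" is an overall allowance for another outcome. Follow-up runs for years and retention measures are described, so loss at month 6 could be lower or higher.
- **That the harm would be missed altogether.** Loss after month 3 leaves the month-3 comparison intact, and nothing restricts the FSFI comparison to month 6.
- **That sexual function is plainly a primary outcome.** Study design and the later outcome lists disagree.

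A further limit concerns baseline. The figures are for month-6 scores, but Study design speaks of change. For change from baseline among returners, with equal SDs, ρ is replaced by the month 3–6 correlation minus the baseline–month 3 correlation. If the two are equal, the bias cancels. With 0.75 and 0.4 as an illustration, it is (0.75 − 0.4) × 1.57 = 0.55 points, so −2.45. The article does not say which quantity would be tested, and relying on this cancellation is not a safe plan.

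**Conclusion.** The point holds in a limited form. The default test for a continuous outcome discards the month-3 scores of women who leave before month 6. It understates month-6 harm when leaving follows a low month-3 score and differs by arm. Under the SD-6 assumptions with score-driven loss in vNOTES only, a true 3 points appears as about 1.8 to 2.6. Under one moderate rule applied to both arms the understatement is about 3–8%, and it vanishes if loss is random or alike in both arms.

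The direction follows from the formula. The size rests wholly on assumed SD, effect, correlation and dropout mechanism. A reader might infer that the plan is bound to hide harm, or that the listed GEE is itself unsound, and the documents support neither. The defect is that the stated default is the weaker method, while a method able to recover the information is optional and unspecified. Because the remedy costs almost nothing and makes no material difference to the estimate when loss is random, the change should be made.

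**What to change.** In the Statistical analysis section, name the main FSFI analysis in place of per-visit two-sample tests: a likelihood-based repeated-measures model on both postoperative visits, with arm, visit, arm-by-visit and baseline FSFI, unstructured covariance and small-sample degrees of freedom. Report the arm differences at months 3 and 6 from this model. Every woman with at least one postoperative score then contributes. Weighted GEE, or multiple imputation using baseline and month-3 FSFI, is an acceptable alternative. If GEE is kept, state its working correlation and weights and remove the discretion over its use for FSFI.

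Add one sensitivity analysis that shifts missing vNOTES scores downward in steps until the conclusion changes. The main model cannot address leaving that depends on the unseen month-6 score itself.

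The cost is a few sentences and a little more analysis work in R, which the article already names. No new data, visits or participants are needed. The change should be fixed before FSFI follow-up data are examined by arm. It removes a bias and does not make the trial large enough for FSFI.

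### Read literally, the general rule for continuous variables sends skewed costs to a Mann–Whitney test with medians, which does not address the difference in mean cost that a cost-effectiveness analysis needs

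*Protocol article*

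**What the plan says.** The protocol article has a short section, Economic evaluation: "A cost-effectiveness analysis will compare hospitalization, surgery, and consumable costs between vNOTES and TU-LESS". It gives the purpose as "Findings will support guideline development and inform patient decision-making". It names no cost estimand, test or interval.

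The Statistical analysis section sets the rule for continuous data: "Continuous variables will be analyzed using t-tests or Mann–Whitney tests". Normal data are summarised by mean and standard deviation, and other data by "medians with interquartile ranges for non-normally distributed data". The threshold is "Statistical significance will be set at *p* < 0.05". Costs are neither named nor exempted. The further methods listed there (propensity matching, Cox regression, GEE and others) are optional tools against bias and are not tied to costs. No bootstrap or mean cost difference with an interval appears.

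**The concern.** A cost-effectiveness analysis rests on the mean cost per patient. Only the mean multiplies up to total spend, and only a difference in means can be the numerator of a cost-effectiveness ratio. A median gives almost no weight to the few expensive cases.

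The null hypothesis of the Mann–Whitney test is that the two distributions are the same. This is not the hypothesis of equal means when the arms differ in shape or spread. Two errors are then possible. The test can call one route dearer when the hospital would spend the same on both, or it can stay silent when one route is dearer because of a minority of costly cases.

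The article gives some reason to think that shapes could differ. Its Background reports fewer perioperative complications but slightly more conversions with vNOTES than with TU-LESS. Its Discussion mentions costly specialised instruments for vNOTES. Instrument cost would move the typical case, while conversions and complications would move the upper tail.

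**Working it through.** The plan gives no cost figure to reproduce, so the check is a simulation.

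**Inputs from the protocol article**
- 36 patients per group (Sample size calculation).
- Significance level 0.05 (Statistical analysis). Sidedness is not stated there; two-sided is assumed.
- vNOTES conversion of 1.83% to 3.07% and 95% expected success in both groups (Sample size calculation). In a group of 36 this is 36 × 0.0183 = 0.7 to 36 × 0.0307 = 1.1 conversions, or 36 × 0.05 = 1.8 at a 5% failure rate.

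**Assumed inputs.** The form and spread of the costs. The usual cost is set to 1.

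**Method.** 10,000 simulated trials per setting, asymptotic Mann–Whitney against the Welch t-test. All entries are rejection rates.

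**1. Lognormal costs.** Each arm is exp(N(−σ²/2, σ²)), so both means equal 1.
- σ = 0.5 in both arms: Mann–Whitney 5%, Welch 5%. With the same shape there is no inflation.
- σ = 0.2 v 0.4: 13% v 5%.
- σ = 0.3 v 0.6: 22% v 6%. The means are equal, but the ratio of medians is exp(−(0.36 − 0.09)/2) = 0.87, and the rank test responds to that.
- σ = 0.3 v 0.6 with equal medians instead, so that the mean ratio is exp(0.135) = 1.145: Mann–Whitney 6%, Welch 14%. A 15% difference in mean cost is almost invisible to the rank test.

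**2. Fixed shift against a small tail, equal means.** Arm A is Normal(1 + pk, CV). Arm B is Normal(1, CV) plus k with probability p. Both means are 1 + pk. With k = 1 the tail cases cost twice the usual, and p is set near the article's conversion and failure rates.

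| Within-arm CV | p = 3%: Mann–Whitney v Welch | p = 5%: Mann–Whitney v Welch |
|---|---|---|
| 10% | 16% v 9% | 33% v 10% |
| 15% | 9% v 6% | 15% v 6% |
| 20% | 6% v 5% | 9% v 5% |
| 30% | 5% v 5% | 6% v 5% |

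With tail cases at three times the usual cost (k = 2), p = 3–5% and CV 15–20%, Mann–Whitney rejects 16–59%, but Welch also rises to 9–13%.

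**3. A real mean difference from the tail alone.** Same model without the shift in arm A, k = 1, p = 3–5%, CV 15–30%: Mann–Whitney rejects 5–6% and Welch 6–11%. Neither test has useful power.

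**The case against.** The strongest objection is that the link is inferred. The Statistical analysis section never mentions costs, and the Economic evaluation section never mentions Mann–Whitney or medians. A health-economic plan or SAP that is not shown may set the method, and leaving it there would be no fault. A reader might infer that the trial has decided to test costs by Mann–Whitney; the documents do not go that far. What stands is narrower: the rule is worded for all continuous variables, and nothing in the text takes costs out of it.

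Second, the harm needs non-normal costs and arms that differ in shape or spread. The article gives no cost distribution. Its Discussion says that costs of the techniques do not differ significantly at this institution, and its sample size section assumes equal success in both groups. If both arms had the same tail, the Mann–Whitney test would keep its level. This part stands, so the error is possible but not shown to be likely.

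Third, a reader might infer a very large error. With 10% of one arm at twice the usual cost, a matching shift in the other and CV 15%, Mann–Whitney rejects 38% under equal means. With a 20% tail in one arm and a real mean difference, its power is about 30% against about 76% for Welch. These tails are well above the conversion rates that the article cites, and complications could raise them only by an amount that it does not give. The documents do not support these figures as the expected size.

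Finally, Welch is not a safe default either: it reached 9–13% in the three-fold tail settings above.

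**Conclusion.** The concern holds in limited form. As written, the general rule would test and summarise non-normal costs in a way that neither tests nor estimates the difference in mean cost per patient. The mechanism works in both directions, but only if the arms' cost distributions differ in shape or spread.

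The size rests on assumed costs, 36 per arm and two-sided 5% tests. Under equal means, a one-arm tail of 3–5% at twice the usual cost gives about 5–15% rejection at CV 15–30%, and 16–33% at CV 10%. Lognormal spread of 0.3 v 0.6 gives 22%, against 6% for Welch. A real difference carried by a 3–5% tail would rarely be found by either test, so the main gain from the change is an estimate of the right quantity, not power.

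Severity is modest. Costs are neither a listed primary nor a listed secondary outcome, and the sample size does not depend on them. The result is nevertheless meant to inform guidelines and patients, so it should be corrected.

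**What to change.** Add one sentence to Economic evaluation or Statistical analysis: costs are exempt from the normality rule, and the cost result is the difference in arithmetic mean cost per randomised patient with a bootstrap 95% confidence interval, whatever the distribution. Medians and interquartile ranges may be shown as description only, with no Mann–Whitney test on costs. If a separate health-economic plan already says this, a cross-reference is enough.

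The change needs no new data, and R is already named. The downside is that the interval will be wide at this sample size, above all if a few very expensive cases occur.

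### The trial is sized on a non-inferiority test of surgical success, but the only stated test that fits that outcome is a chi-square or Fisher test of equality

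*Protocol article*

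**What the plan says.** Three places in the protocol article bear on this.

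- **Sample size calculation.** "A one-sided non-inferiority test was used to determine the sample size". vNOTES is taken to remain the preferred option "despite a potential 15% lower success rate compared to TU-LESS". The resulting size is given as follows: "To achieve 85% power for non-inferiority with a 95% expected success rate in both groups, a total of 54 cases were required". After a dropout allowance this becomes 72, or 36 per arm. No alpha is given here.
- **Primary short-term outcome.** "Completion of surgery using the allocated technique is Primary short-term outcome". This is a yes/no variable, and it is the success rate on which the trial was sized.
- **Statistical analysis.** "Categorical variables will be analyzed using chi-square or Fisher’s exact tests", and "Statistical significance will be set at *p* < 0.05", with no sidedness. The other methods listed are propensity score matching, stratification, multivariate analysis, Cox regression, GEE and a logistic model for risk factors for conversion. None is tied to a margin.

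Non-inferiority and the 15% figure appear only in the sample size section.

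**The concern.** A chi-square or Fisher test asks whether the data are compatible with no difference. A non-inferiority test asks whether they rule out a deficit as large as the margin. With 36 per arm and success near 95%, the two questions often have different answers. The general rule for categorical variables makes no exception for completion. A reader who applies it to that outcome obtains a p-value that cannot support the conclusion for which the trial was sized.

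At stake is the main short-term claim. If no margin-based rule is on record before the data are seen, any later statement that vNOTES is non-inferior rests on a test that the public plan did not name.

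**Working it through.** **Inputs.** From Sample size calculation: 95% expected success in both arms, a 15% margin, 85% power, 54 evaluable (27 per arm), 72 in total (36 per arm). From Statistical analysis: chi-square or Fisher, p < 0.05. Assumptions: the margin is 15 absolute percentage points; alpha is one-sided 5% or 2.5%, both shown.

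**1. The plan's own figure.** With the usual normal approximation,

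n per arm = 2 × 0.95 × 0.05 × (z₁₋α + z₀.₈₅)² / 0.15²

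- One-sided 5%: 0.095 × (1.645 + 1.036)² / 0.0225 = 30.4, so 31 per arm, 62 in total.
- One-sided 2.5%: 0.095 × (1.960 + 1.036)² / 0.0225 = 37.9, so 38 per arm, 76 in total.

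The stated 54 does not reproduce at 85% power. It matches 80% power at one-sided 5% (27 per arm). That is a separate matter, and nothing below depends on it. The formula is a margin formula, which confirms that the sizing hypothesis was non-inferiority.

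**2. How often the difference test is non-significant when vNOTES is worse by the full margin.** Sum the product of the two binomial probabilities over all possible results, with true success of 80% (vNOTES) and 95% (TU-LESS) and 36 per arm:

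| Rule | Share of trials |
|---|---|
| Fisher p ≥ 0.05 | 65.5% |
| Uncorrected chi-square p ≥ 0.05 | 47.1% |
| Newcombe lower limit above -15 points, one-sided 5% | 4.7% |
| Newcombe lower limit above -15 points, one-sided 2.5% | 2.3% |
| Wald lower limit above -15 points, one-sided 5% | 7.2% |
| Wald lower limit above -15 points, one-sided 2.5% | 4.5% |

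The last four rows are the chance of wrongly declaring non-inferiority. If the 15% were relative, true success would be 0.85 × 95% = 80.75%. The first two rows would then be 68.9% and 50.2%.

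**3. One result that separates the two questions.** Take 31/36 (86.1%) on vNOTES and 34/36 (94.4%) on TU-LESS.

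- Difference: -8.3 points. Fisher p = 0.43; uncorrected chi-square p = 0.23.
- Newcombe, one-sided 95%: the Wilson lower limit for 31/36 is 74.1% and the Wilson upper limit for 34/36 is 98.1%. The lower limit of the difference is -0.0833 - √[(0.8611 - 0.7410)² + (0.9814 - 0.9444)²] = -0.0833 - 0.1257 = -0.209, or -20.9 points.

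Non-inferiority at 15 points is not shown. With 34/36 in both arms, Fisher gives p = 1.00 and the same limit is -10.6 points, so non-inferiority is shown. Both results are non-significant on the difference test, and only the margin test tells them apart.

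**4. Power of the margin test when both arms truly succeed in 95%.**

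| Evaluable per arm | Newcombe, one-sided 5% | Newcombe, one-sided 2.5% |
|---|---|---|
| 36 | 78.6% | 65.3% |
| 27 (the plan's 54) | 61.8% | 55.5% |

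**The case against.** The strongest reply is that the Statistical analysis section is one generic paragraph in a condensed article. It gives default tests by type of variable, does not name the primary outcome, and does not call chi-square or Fisher the primary analysis. A statistical analysis plan that is not shown may contain a margin test, and the interval method and decision rule are often left to such a plan.

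Part of this stands, and it rules out several stronger readings that a reader might infer:

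- **That the trial will never test non-inferiority.** The article does not show this. It shows only that the stated analysis does not.
- **That a non-significant p will be presented as proof that vNOTES is as good.** Nothing in the article says so. The figures show why such a reading would be unsafe, not that it is planned.
- **That the difference test would usually miss a deficit equal to the margin.** This holds for Fisher (65.5%) but not for uncorrected chi-square (47.1%), and the article does not say which applies.
- **That the whole analysis is unsound.** The mismatch concerns completion with the allocated technique. No margin is stated for pregnancy, delivery or incisional complications, and the listed tests are conventional for those.

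What does not stand is the view that this is merely omitted detail. The article is not silent: it assigns a test to every categorical variable, and that test does not match the hypothesis in its own sample size section.

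**Conclusion.** The mismatch is real and should be corrected before the data are analysed. The sample size section commits to a one-sided non-inferiority comparison of success, while the only stated test that fits this two-arm binary outcome tests equality. The gap is large in practice. When vNOTES is worse by the full margin, non-significance occurs in roughly half to two thirds of trials of this size, against at most about 5% wrongly passed by a Newcombe bound.

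The sizes rest on 36 evaluable patients per arm, an absolute 15-point margin and an assumed one-sided alpha of 5% or 2.5%. The existence of the mismatch rests on none of these.

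**What to change.** Add to the Statistical analysis section that completion with the allocated technique will be analysed as the difference in completion rate, vNOTES minus TU-LESS, with patients counted in their allocated arm. State the one-sided alpha, and that the margin is 15 absolute percentage points if that is what was meant. Use a Newcombe or score-type interval (two-sided 90% for one-sided 5%, two-sided 95% for one-sided 2.5%), and claim non-inferiority only if the lower limit is above -15 points. A Wald interval is less suitable at success rates this high, because its error exceeds the nominal level under both alphas. Keep chi-square or Fisher for the other categorical outcomes.

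The text costs one paragraph and no extra data. The real cost is that the power of the proper test becomes explicit: with Newcombe about 79% or 65% at 36 per arm, and about 62% or 56% at the plan's evaluable 27 per arm, for one-sided 5% and 2.5% respectively. All are below the stated 85%. The sponsor should see these figures before fixing alpha.
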